**Qualitative Interviews for process evaluation**

A total of 20 patients of the intervention group and 10 intervention patients’ physicians (first patients or physicians who agree to participate) are surveyed 5.5 months after telephone-intervention (shortly before t2-measurement) in semi-structured 20- to 30-min telephone-interviews by psychologists of the project team. Patients are interviewed on their acceptance and perception of the telephone-intervention and accompanying materials as well as on the feasibility (e.g. experience in implementation, helpful factors and barriers) of intervention contents. Physicians are asked for their subjective evaluation of the intervention (e.g. usefulness, improvement suggestions). Interviews will be audio-recorded with the permission from participants.

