**Procedure**

The chosen outcomes for patients are measured prior to the intervention (baseline measurement, t0), directly after the intervention (t1) and after a 6-month follow-up period (t2).

At t0, patients in the intervention group are sent paper-pencil pseudonymized questionnaires on baseline proximal and distal secondary outcomes and socio-demographic information. Upon receipt of the filled questionnaires, telephone appointments are arranged with patients for a study physician interview by study nurses. During telephone calls, a vaccination history, use and availability of stand-by antibiotics and the medical alert card are taken to gather baseline data on the primary outcome, the PrePSS-score, along with some other medical information relating to the patients’ asplenia (e.g. indication for splenectomy, splenectomy date and previous episodes of infection or PSS requiring hospitalization)

After t0-data collection, the patient-directed telephone-intervention is implemented. The intervention of the corresponding physician is conducted at about the same time; however, the order is determined by the arrangement of the telephone appointments and not standardized. Secondary physician outcomes are gathered after the physician-directed intervention. Historical control group patients and their physicians go through the same procedure and patients receive t0-questionnaires identical to intervention group patients, but only intervention participants continue measurement after the telephone intervention.

Following each patient telephone call, intervention patients complete post-intervention questionnaires on the proximal secondary outcomes similar to baseline items and evaluate the telephone-intervention (t1).

To test for six-month sustainability of the effects of the intervention they receive follow-up questionnaires on distal secondary outcomes identical to baseline measurement (t2). After return of the follow-up questionnaires, intervention patients are contacted by study physicians via telephone again to inquire the same set of data on the primary outcome and (changes in) medical data, such as the incidence of infections and PSS, gathered at t0.

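### Process interviews with 20 intervention patients shortly before t2 can nudge the primary outcome upward in one arm; they should follow the t2 PrePSS call

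*Protocol*

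**What the plan says.** The Protocol section Qualitative Interviews for process evaluation plans semi-structured telephone interviews of 20 to 30 minutes, conducted by project psychologists, with "A total of 20 patients of the intervention group and 10 intervention patients’ physicians". They are the "first patients or physicians who agree to participate", and they "are surveyed 5.5 months after telephone-intervention (shortly before t2-measurement"). Patients are asked about their acceptance and perception of the session and materials, "as well as on the feasibility (e.g. experience in implementation, helpful factors and barriers) of intervention contents". For physicians the content is narrower: "Physicians are asked for their subjective evaluation of the intervention (e.g. usefulness, improvement suggestions").

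The Procedure section places the last measurement "after a 6-month follow-up period (t2"). Its purpose is stated as "To test for six-month sustainability of the effects of the intervention". Once the t2 questionnaires are back, "intervention patients are contacted by study physicians via telephone again to inquire the same set of data on the primary outcome", and the answers are confirmed with the physician. Controls contribute t0 data only. Data analysis compares the follow-up PrePSS-score of the intervention group with the control group, using a general linear model with the propensity score as covariate.

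**The concern.** The interview falls about two weeks before the six-month point, and the PrePSS call comes later still because it waits for the questionnaires. For the interviewed patients, the t2 score is thus taken soon after a fresh conversation about the behaviours that it measures.

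The protocol's own theory makes some prompting plausible. The section on the patient-directed intervention lists follow-up prompts among its behaviour change techniques, makes work on personal barriers part of the planning section, and includes a later call that monitors measures and discusses barriers. Contact of a similar kind cannot simply be assumed inert when it is called process evaluation.

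Any effect would run one way. It could raise the intervention mean and not the control mean, so it favours the tested hypothesis. The propensity score adjusts for covariate differences between the groups; it cannot remove a contact made during follow-up in one arm. The distal secondary outcomes at t2 are exposed in the same way, and the cost-effectiveness analysis would credit any gain to the intervention without the interview being part of it.

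**Working it through.** **Order of events (intervention arm).** t0 data, telephone session, t1 questionnaire, process interview at 5.5 months (20 patients), t2 questionnaire at 6 months, PrePSS call, physician confirmation. The gap from interview to t2 is 6 − 5.5 = 0.5 months, plus questionnaire return time. Controls: t0 data, then a shortened session; nothing measured afterwards.

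**Where the score can move in that time.** Table 1 gives 3 + 3 = 6 points to the two vaccination items and 2 + 2 = 4 points to the stand-by antibiotic and alert card. Two weeks leaves most room on the latter 4 of 10 points and less on sequential vaccination.

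**The plan's own figure.** Sample size considerations: effect size 0.40, 80% power, two-sided 5%. The normal formula gives 99 per group and the t-test 99.1, so the stated 100 per group is reproduced.

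**Share of the arm interviewed.**
- Stated analysis sample: 20/178 = 11.2%.
- Sample implied by the stated rates: 500 × 0.5 × 0.6 = 150, and 20/150 = 13.3%.
- Minimum sample: 20/100 = 20%.

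**Shift in the arm mean.** Shift = (20 / n in the intervention arm) × b, where b is the interview effect in SD among those interviewed. The protocol gives no b, so 0.2, 0.4 and 0.8 are assumed.

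**Type I error with no true intervention effect.** SE = √(1/n₁ + 1/n₂) in SD units, and error = Φ(shift/SE − 1.96) + Φ(−shift/SE − 1.96). For 178 vs 110, SE = √(1/178 + 1/110) = 0.121. At b = 0.4 the shift is 0.112 × 0.4 = 0.045.

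| Groups | b (SD) | Shift (SD) | Share of 0.40 | Type I error |
|---|---|---|---|---|
| 178 vs 110 | 0.2 | 0.022 | 5.6% | 5.4% |
| 178 vs 110 | 0.4 | 0.045 | 11.2% | 6.6% |
| 178 vs 110 | 0.8 | 0.090 | 22.5% | 11.5% |
| 150 vs 100 | 0.2 | 0.027 | 6.7% | 5.5% |
| 150 vs 100 | 0.4 | 0.053 | 13.3% | 7.0% |
| 150 vs 100 | 0.8 | 0.107 | 26.7% | 13.1% |
| 100 vs 100 | 0.2 | 0.040 | 10.0% | 5.9% |
| 100 vs 100 | 0.4 | 0.080 | 20.0% | 8.7% |
| 100 vs 100 | 0.8 | 0.160 | 40.0% | 20.5% |

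The 100 controls in the middle rows are 500 × 0.4 × 0.5 from the stated control-group rates.

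**Limit.** For the interviews alone to produce the planned 0.40 SD, b would have to be 0.40 / (20/178) = 3.6 SD.

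**The case against.** The case for leaving the schedule alone has substance. The interview is not a second dose of the intervention: the session, given by infectious disease physicians, informs, motivates, sets goals and builds plans, whereas the interview, given by psychologists, asks for opinions and experience, with no teaching or re-motivation described. Only the talk about implementation and barriers overlaps. The intervention already has an optional follow-up call on barriers, so only the increment beyond that is unplanned. Participants are sent the alert card before the session, so room for change lies mainly with patients who had not acted in 5.5 months. All of this stands, and it argues for a small effect; it does not argue for none, nor does it give a reason for interviewing before t2.

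Three stronger readings are tempting, and the protocol does not support them.

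- A reader might infer that the whole arm gets a booster. Only 20 patients and 10 physicians are interviewed, and a booster effect is an inference, not a documented fact.
- A reader might infer that interviewed physicians will be moved to complete vaccinations, which would extend the reach to 30 patients. Physicians are asked only to evaluate the intervention, so this route is weaker.
- A reader might infer a large bias in score points: 30 of 150 patients gaining 2 points each would raise the mean by 0.20 × 2 = 0.40 points. That stacks worst cases: a uniform 2-point gain, ten further patients reached through physicians, and the smaller sample.

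**Conclusion.** The point holds as a small, one-directional and avoidable bias. The timing, the contact in one arm only, and its place before the primary outcome call are all fixed by the protocol. That the interview changes behaviour is plausible on the protocol's own theory but not shown. With 20 of 178 patients reached, 110 controls and an assumed interview effect of 0.2 to 0.8 SD, the shift is about 0.02 to 0.09 SD, or 6% to 22% of the planned effect, and the type I error is about 5.4% to 11.5%. The upper end rests on a generous effect for a single evaluative call.

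The interviews could not plausibly create the planned effect by themselves, nor do they void t2 as a test of sustainability for the arm as a whole. The calculation assumes equal unit SD, a normal test without propensity adjustment, and the same interview effect in all 20 patients.

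**What to change.** In Qualitative Interviews for process evaluation, place each patient interview after that patient's t2 questionnaire and PrePSS call, and each physician interview after the t2 confirmation of that physician's data. The cost is slightly longer recall, and patients lost before t2 would not be interviewed, so the process evaluation would hear only from those who reached t2.

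If interviews have already been held, add a sensitivity analysis of the primary outcome without the interviewed patients. This is a weak fallback: interviewees are the first who agree, so leaving them out changes the mean through self-selection as well as through any prompting, and a difference could not be attributed to prompting alone.

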**Data analysis**

Demographic characteristics of the study population and effect sizes in the intervention group will be reported descriptively. The main analysis tests the hypothesis that the PrePSS-score at follow-up is higher (better adherence to infection-risk reducing preventive measures) in the intervention group than in the control group. Due to the non-randomized design a propensity score adjustment is performed to reduce potential bias that may be caused by differences on covariates in the two groups (36). We will apply general linear models with propensity score as a covariate. The same method will be used for the analysis of secondary outcomes. Assuming missing data in the questionnaires, multiple imputation will be considered for corresponding analyses. Additional analyses will be conducted with structural equation modeling technique to test a priori specified mediation models of intervention effects.

A cost-effectiveness analysis of the intervention will be conducted by analyzing the change-from-baseline scores of the primary and the secondary outcomes in relation to the costs of the intervention. To reveal the economic efficiency of the intervention, routine data will be used to determine standard treatment and follow-up costs associated with infections requiring hospitalization and with PSS in asplenic patients to contrast them to the intervention costs.

In the qualitative analyses, the audio files of the interviews will be transcribed by an external service provider and the transcripts will be analyzed using a qualitative content analysis.

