**Sample size considerations**

A priori calculation of the sample size of patient participants to compare the intervention group to the historical control group in the primary outcome was performed with the software ‘*Power and Precision*‘*.* Based on an assumed medium to large effect size of 0.40, a statistical power of 80% and a significance level of 5% (two-sided) the minimum required patient sample of *N* = 100 per group was calculated. Further sample size considerations take into account the actual number of splenectomized patients insured by the AOK. An explorative request showed that 360-400 patients undergo splenectomy a year, resulting in approximately 500 patients assumed to be available for recruitment in the planned inclusion period of 18 months. Based on studies with similar patients (13), we further estimated a proportion of 50% non-respondents for the intervention group and attrition rates of 40% of respondents, so we aim to recruit 500 potential intervention group patients for an expected analysis sample of *N* =178 participants. As this exceeds the statistically required number of cases despite conservative estimations, sufficient cases will be available even after considering potential deceases in the course of the study.

Given that the inclusion period (18 months) is the same for the control group (although retrospectively), sample size considerations for this group are largely the same, with the exception of an assumed proportion of 60% non-respondents and a dropout rate of 50%, resulting in expected *N* = 110 control group cases for analysis. Correspondingly, the number of physician participants included in analysis will be *N* = 178 intervention patients’ physicians and *N* = 110 control patients’ physicians maximum, considering that some patients may have the same physician.

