# Discussion

Poor implementation of the prevention recommendations for patients without a functioning spleen has been demonstrated in several studies. Better adherence to preventive measures is urgently needed (2, 11). However, conclusive and effective new strategies to improve care beyond the passive provision of information have not yet been described for asplenic patients.

Strengths of the current study are the development and evaluation of a theory-based dual intervention, i.e. focusing on patients and their physicians. By educating and training patients, the intervention contributes to the empowerment of the patients. Quantitative data will allow us to evaluate the effect of the intervention on prevention measures such as vaccinations, prophylactic and stand-by antibiotic use and patient-related outcomes*.* Qualitative interviews will enable us to understand e.g. barriers in preventive behaviour. Furthermore, the new intervention can be improved on the basis of feedback from asplenic patients and their physicians. Following this evaluative process, the intervention-manual will be made publicly available on the German website ‘asplenie.net’ to enable future implementation in practice.

The study has some limitations, which are mainly based on our sampling strategy. First, our sample contains a self-selected group of patients from the cooperating health insurance (AOK Baden-Württemberg). Secondly, it is not a randomized controlled trial, however, due to above outlined ethical reasons randomization is not justifiable. In order to reduce a potential bias that may be caused by differences in covariates in the intervention vs. historical control group, propensity score matching will be applied. Third, the primary outcome, the PrePSS-score was developed via expert-ratings, however, weighting of the four included items may still need further refinement and research.

All in all, we believe that the experience gained with this type of intervention will also be very valuable for prevention strategies in patients with other diseases. The intervention could be considered - after demonstrated effectiveness - in the context of other poorly implemented primary prevention measures or standard vaccinations, e.g. influenza and pneumococcal vaccination in patients over the age of 60 years.

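### With only an estimated propensity score as covariate, the ordinary model standard error is conservative if the covariates are prognostic; add those covariates or bootstrap, and settle adjustment versus matching

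*Protocol*

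**What the plan says.** The Data analysis section gives the reason for adjusting: "Due to the non-randomized design a propensity score adjustment is performed to reduce potential bias". It then fixes the model: "We will apply general linear models with propensity score as a covariate". For the rest it adds: "The same method will be used for the analysis of secondary outcomes". It does not list the covariates that will build the score or say how the standard error will be obtained.

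The Discussion, listing limitations, describes a different method: "propensity score matching will be applied".

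Sample size considerations assumes a standardised effect of 0.40, 80% power and a two-sided 5% test. On that basis "the minimum required patient sample of *N* = 100 per group was calculated". The section plans "for an expected analysis sample of *N* =178 participants" in the intervention group and 110 in the control group.

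**The concern.** A propensity score estimated from the trial's own data removes chance imbalance in every covariate used to build it. The group estimate is therefore about as precise as one from full covariate adjustment. But the score predicts group membership, not the PrePSS-score. Most of the outcome variance that the covariates could explain stays in the residual of a model holding only group and score. The standard error that such a model prints belongs to a less precise estimator than the one actually used.

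At stake is the calibration of the primary confidence interval and p-value, and of every secondary comparison. Intervals would be wider than needed, the nominal 5% test would run at a stricter level that nobody chose, and power already present in the data would be given up.

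**Working it through.** **1. The plan's own figure.** With effect 0.40, two-sided 5% and 80% power, the normal approximation gives n = 2 × (1.960 + 0.842)² / 0.40² = 2 × 7.85 / 0.16 = 98.1, so 99 per group. The t-test solution is 99.08, so 100. Power at 100 per group is 80.4%. The stated 100 is reproduced. It is an unadjusted two-group calculation.

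**2. Large-sample size of the effect.** Let R² be the share of within-group outcome variance explained by the propensity covariates but not captured by the score. The protocol gives no value, so R² is an assumption and is shown as a range. With equal variances:

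- model SE / true SE = 1 / √(1 − R²)
- true test level = 2 × [1 − Φ(1.96 × ratio)]

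| R² | ratio | SE too wide by | true test level |
|---|---|---|---|
| 0 | 1.000 | 0% | 5.0% |
| 0.08 | 1.043 | 4.3% | 4.1% |
| 0.10 | 1.054 | 5.4% | 3.9% |
| 0.20 | 1.118 | 11.8% | 2.8% |
| 0.30 | 1.195 | 19.5% | 1.9% |

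**3. Simulation.** Assumptions: linear additive outcome model, 8 covariates, logistic propensity score entered linearly, equal variances unless stated, independent patients.

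- *Imbalance of 0.5 SD in a random direction, 178 vs 110, covariates explaining 10/20/30% of variance:* SE ratio 1.04/1.12/1.19, test level 4.3/2.7/1.9%.
- *Imbalance of 0.5 SD fully aligned with prognosis:* ratio about 1.01-1.06, level 3.9-4.6%. Here the score itself carries most of the prognostic information. With alignment of 0.9 and 30% explained, the ratio was 1.08 and the level 3.6%.
- *Covariates not prognostic:* ratio 1.00, level 5.2%.
- *Control SD 1.3-1.5 times the intervention SD, 178 vs 110:* ratio 0.91-0.98, level 4.7-7.1%. The smaller group is the more variable one, and this works against the conservatism.
- *Intervention SD 1.4 times the control SD:* ratio 1.17, level 2.6%.

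The estimate showed no material bias in these runs. Its empirical SD agreed with that of full covariate adjustment to within 0.0003, which confirms the mechanism. With equal variances, entering the covariates gave levels of 4.3-5.5%. A heteroscedasticity-robust standard error alone did not help: at 30% explained it gave 2.3%, the same as the ordinary one.

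**4. Power at effect 0.40 (10/20/30% explained).**

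| Sample | score only | score + covariates | loss in points |
|---|---|---|---|
| 178/110, first set | 0.90/0.92/0.92 | 0.92/0.94/0.96 | 2/2/4 |
| 178/110, second set | 0.906/0.923/0.942 | 0.922/0.950/0.975 | 1.6/2.7/3.3 |
| 100/100, first set | 0.77/0.80/0.81 | 0.80/0.85/0.89 | 3/5/8 |
| 100/100, second set (30% only) | 0.830 | 0.905 | 7.5 |

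With aligned imbalance, score-only power at 100 per group reaches about 0.87, because the score then removes outcome variance itself.

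The 100-per-group rows matter. The protocol's own rates give 500 × 0.5 × 0.6 = 150 and 500 × 0.4 × 0.5 = 100, not 178 and 110, which puts the control group at the stated minimum.

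**5. Is R² above zero plausible here?** The protocol expects disease knowledge to be a confounder. It collects other potentially confounding variables, including compliance items that cover having vaccinations done. Vaccination carries 3 + 3 = 6 of the 10 PrePSS points. This supports some prognostic content but does not give its size.

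**The case against.** The protocol fixes a point-estimation model and names no standard error. A bootstrap or another correction could properly sit in a statistical analysis plan that is not shown. That stands: a reader might infer that the protocol commits to a wrong standard error, and it does not say so. The point is therefore conditional on the ordinary one being used.

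A reader might also infer that the standard error is too wide whatever covariates are chosen. The runs do not support this. The excess vanishes with non-prognostic covariates. It is small when imbalance is aligned with prognosis, which is the confounding that motivates the adjustment. It can reverse when the control group is more variable. None of the covariates, their R² or the group variances is in the protocol.

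Nor do the figures show a biased or underpowered trial. The error is towards caution, and power at the expected sample sizes stays near 0.90 or above.

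Finally, the main remedy can be called ANCOVA under another name: in the runs, the covariates explained 96-99% of the score's variance, and power matched covariate adjustment without the score (0.961 against 0.963). That is fair, but it is no argument against the change. The covariates are needed for the score anyway, and entering them calibrates the test under equal variances and lowered power in none of the settings examined.

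**Conclusion.** The concern holds conditionally. It is a matter of efficiency and calibration, not validity. It rests on the ordinary standard error, a linear model, equal variances, independent patients, and covariates explaining 10-30% of PrePSS-score variance. The standard error is then about 4-19% too wide when imbalance is mostly unrelated to prognosis and about 1-6% too wide when it is aligned. The corresponding test levels are about 2-4% and 4-4.6%.

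Power is about 0.77-0.87 at 100 per group and about 0.90 or more at 178/110, so the planned 80% is broadly kept. What is given up is about 1-4 points at 178/110 and up to about 7-8 points at 100 per group. Separately, the Data analysis section and the Discussion name different propensity score methods. If matching is what is meant, these figures do not apply.

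**What to change.** State the model as group, propensity score and the prognostic covariates used to build it, for the primary and secondary outcomes. This costs about 8 degrees of freedom under the simulated set-up, out of 178 + 110 = 288 patients, and needs no new data.

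If the score is to remain the only covariate, take the confidence interval and p-value from a bootstrap stratified by group that re-estimates the score in each resample. In one check (178/110, 30% explained) the true SD was 0.102, the model SE 0.126 and the bootstrap SE 0.105. The extra cost is programming, including a rule for combining the bootstrap with the multiple imputation under consideration.

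Adding covariates does not cure unequal variances. With a control SD 1.3-1.5 times larger, the ordinary standard error in the fuller model still gave test levels of 6.6-7.3%. If unequal spread is expected, pair that model with a heteroscedasticity-consistent standard error.

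Reconcile the Discussion with the Data analysis section, so that one propensity score method is named throughout.
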